### Secondary analysis

1. Descriptive statistics stratified by mutation will be used to report stage and grade of prostate cancer.

2. Sensitivity, specificity, positive and negative predictive value of: PSA, free to total PSA, prostate MRI in detecting prostate cancer among men with genetic predispositions will be calculated.

3. A Receiver Operating Curve (ROC), and calibration and decision curve analyses will be performed for each of the aforementioned screening tests. The threshold for biopsy for each test will be calculated based on any prostate cancer detected as well as clinically significant cancer detected (for the purpose of this study any cancer with a Gleason sum equal or higher than 7 will be considered clinically significant).

4. We will use a Markov model to establish the cost effectiveness of different screening tests (PSA, free to total PSA, prostate MRI) in detecting prostate cancer and clinically significant prostate cancer among men with genetic predispositions.

5. Descriptive statistics stratified by mutation will be used to report the impact of these genetic mutations on lower urinary tract symptoms (IPSS, flow and post void urine residual) and BPH (trans-rectal US prostate size).

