### Statistics

#### Primary analysis

The primary aim of this study is to estimate the true prevalence of prostate cancer among men with genetic predisposition. Since our study will offer a prostate biopsy to all subjects upon entry we will avoid “verification bias” associated with PSA based screening. However, this fact prevents us from including a control group, as we feel it may be unethical to offer non-carrier such a work-up. Therefore, we will use descriptive statistics only to report the primary outcome stratified by mutation. The fact that we are not including a control group also prevents us from providing a sample size calculation. We will perform a preliminary analysis of our data after 220 patients.

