## Discussion

The only ongoing study specifically designed to test PSA screening among BRCA Carriers is the IMPACT study
[20,27]. The IMPACT study, led by [name], is a multicenter observational study of screening for prostate cancer. In this study, male BRCA carrier’s, 40 to 69 years old, are offered annual PSA testing and the threshold for prostatic biopsy is any PSA higher than 3 ng/ml. Recently, the first round of screening was published
[25]. In this study, a total of 199 men (8%) presented with PSA >3.0 ng/ml, 162 biopsies were performed, and 59 PCas were diagnosed (18 BRCA1 carriers, 10 BRCA1 controls; 24 BRCA2 carriers, 7 BRCA2 controls); 66% of the tumors were classified as intermediate- or high-risk disease. A final report is expected in 2018.

The proposed study, although targeting a similar population, is different in several important aspects. First, in the IMPACT study only patients with an elevated PSA level are offered a prostate biopsy. In a preliminary report on the first round of screening, only 8% had a biopsy
[25]. The fact that only such a small percentage of patients were offered a biopsy, and that it was offered based on PSA levels may cause a “verification-bias”
[27,28].

Verification bias is a type of measurement bias. This bias occurs when results of a screening test (i.e. PSA) affect whether a diagnostic test (i.e. prostate biopsy) is used. Results from the PCPT trial
[29], which offered prostate biopsy to all subjects (independent of their PSA level), demonstrated that as many as 15% of men with a PSA value less than 3.0 ng/mL had prostate cancer and that 15% of these cancers were high grade. These results may be even more pronounced in a population of high-risk men with germline mutations. To eliminate this bias, we will offer a prostate biopsy to all men included in the study regardless of the PSA level.

The second notable difference between our study and the IMPACT study is the target population. Our institution is located in Israel where the predominant BRCA mutations are the three founder mutations. There is evidence to suggest a genotype-phenotype difference among BRCA founder mutation carriers compared to other germ-line mutations
[30,31]. In addition, since 2% of Ashkenazi Jews carry one of the founder mutations we will have enough power to detect a difference in prostate cancer parameters between the three mutations
[31].

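### Biopsy thresholds are calculated from the same cancers used to report test accuracy, so sensitivity at those thresholds will be overstated, most of all for clinically significant cancer

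*Protocol article*

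**What the plan says.** Item 2 of the protocol's Secondary analysis lists the accuracy measures: "Sensitivity, specificity, positive and negative predictive value of: PSA, free to total PSA, prostate MRI in detecting prostate cancer". It gives no value at which any test counts as positive. Item 3 adds "A Receiver Operating Curve (ROC), and calibration and decision curve analyses will be performed for each of the aforementioned screening tests" and then says how the thresholds arise: "The threshold for biopsy for each test will be calculated based on any prostate cancer detected as well as clinically significant cancer detected". The second target is defined there too: "any cancer with a Gleason sum equal or higher than 7 will be considered clinically significant". With three tests and two targets, six thresholds are to be derived from this cohort.

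No other cut-off is adopted. The MRI description gives a five-point Likert scale without saying which score is positive. The one PSA biopsy cut-off in the text, 3 ng/ml, describes another screening study (Discussion).

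On numbers, Primary analysis says "The fact that we are not including a control group also prevents us from providing a sample size calculation" and then "We will perform a preliminary analysis of our data after 220 patients". No final sample size or expected number of cancers is given.

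**The concern.** A threshold chosen because it separates cancers from non-cancers well in one sample exploits that sample's chance features. Sensitivity calculated at that threshold in the same men is then too high on average. Sensitivity rests on the cancers alone, so the bias grows as they become fewer. Specificity rests on the many men without cancer and hardly moves.

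Two things are at stake. First, overstated sensitivity means understated missed cancers, and the error is largest for Gleason 7 or more, where events are scarcest. Second, the Discussion says the study will settle which screening method is best. A continuous marker offers many candidate cut-offs and a five-point score only four, so the continuous marker gains more from the search. Two equally good tests would not look equal.

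**Working it through.** The protocol states no accuracy, power or sample-size figure, so there is nothing of its own to reproduce. The check has two parts: how many cancers to expect, and how large the bias is at those counts.

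**Inputs**
- Men: 220, from Primary analysis (preliminary-analysis count).
- Prevalence: 10–15%, an assumption. The upper value borrows the cited figure of "as many as 15% of men with a PSA value less than 3.0 ng/mL had prostate cancer", which comes from men not selected as carriers. The lower value has no source in the protocol.
- Share of cancers that are significant: 15–66%, an assumption. The Discussion gives 15% high grade in the study that biopsied men regardless of PSA, and 66% intermediate or high risk in the PSA-triggered study. The latter is a different definition from Gleason 7 or more.
- All men biopsied: an assumption. Biopsy is offered and may be declined, which would reduce the counts.
- True AUC 0.70 (also 0.65 and 0.80) and the Youden rule: assumptions. The protocol names neither.

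**Expected cancers**
- Any cancer: 220 × 0.10 = 22; 220 × 0.15 = 33.
- Gleason 7 or more: lowest 22 × 0.15 = 3.3; highest 33 × 0.66 = 21.8. That is about 3 to 22. Taking 33 × 0.15 gives about 5.

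**Bias**

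The marker is normal with unit variance in both groups, with mean 0 without cancer and d with cancer, where d = √2 × Φ⁻¹(AUC). For AUC 0.70, d = 1.414 × 0.524 = 0.74. In each simulated cohort of 220 the cut-off maximising sensitivity + specificity is found. Its apparent values are compared with its true values, 1 − Φ(c − d) for sensitivity and Φ(c) for specificity. At least 2,000 cohorts were run per setting.

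Continuous marker, AUC 0.70:

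| Cancers | Apparent sensitivity | True sensitivity | Excess |
|---|---|---|---|
| 33 | 70% | 62% | 8 points |
| 22 | 71% | 61% | 10 points |
| 10 | 76% | 60% | 16 points |
| 5 | 81% | 57% | 23 points (from unrounded values) |

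Over AUC 0.65 to 0.80 the excess is 7–8 points with 33 cancers and 21–24 points with 5. Specificity is overstated by about 1 point at most (0.002 to 0.011).

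Five-category score (four possible cut-offs), AUC 0.70: the sensitivity excess is about 3 points with 33 cancers, 5 with 22 and 13 with 5.

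**Effect on the comparison**

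Take two tests with the same AUC of 0.70 and 22 cancers. Youden index = sensitivity + specificity − 1.
- Continuous marker: apparent 0.714 + 0.661 − 1 = 0.375; true 0.614 + 0.652 − 1 = 0.266.
- Five-category score: apparent 0.668 + 0.642 − 1 = 0.310; true 0.622 + 0.638 − 1 = 0.260.

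The apparent gap is 0.065 and the true gap 0.006. Most of the apparent advantage comes from the threshold search.

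**With a cut-off fixed beforehand**

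With 5 cancers and AUC 0.70, the bias is +0.0003 for sensitivity and +0.0003 for specificity, in effect zero. Imprecision remains: the 95% Wilson interval is 0.38–0.96 for 4 of 5 cancers detected and 0.62–0.89 for 26 of 33.

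**The case against.** The strongest reply is that an article condenses a plan. Cut-offs, the threshold rule and internal validation commonly sit in an analysis plan that is not shown. That is right as far as it goes: the absence of a bootstrap here is not an error in itself. The point rests instead on what item 3 positively states, that thresholds come from this cohort's cancers. An unseen plan could correct for that, but the protocol as written makes derived thresholds the only ones.

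Other parts of the reply also stand:
- The protocol does not say outright that item 2 is evaluated at the item 3 thresholds. That is an inference, drawn because no other cut-off is offered.
- No Youden rule is named. Decision curves are planned, so a threshold could come from a risk level or a target sensitivity. The sizes above belong to one assumed rule.
- 220 is not a final sample size. With 33 or more cancers the bias is moderate.
- Estimating carrier-specific thresholds is a reasonable aim, since the protocol says evidence on PSA in carriers is very limited. It is an argument for keeping the derived thresholds as exploratory results.

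Two stronger readings are tempting and unsupported. A reader might infer that calibration will look perfect by construction. The protocol says only that "calibration and decision curve analyses will be performed for each of the aforementioned screening tests" and does not say where the predicted probabilities come from. A logistic model refitted to its own data gave intercept 0 and slope 1 in every run, but a grouped plot from a misspecified model still showed failure (lowest tenth: 10.2% predicted, 3.2% observed), and an existing risk model could also be seen to miscalibrate. A reader might also infer that these accuracies are the stated inputs to the Markov model. Item 4 does not list its inputs.

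**Conclusion.** The point holds for sensitivity. Item 3 commits to cohort-derived thresholds, accuracy is reported in the same men, and nothing else in the protocol supplies a cut-off. Under the stated assumptions the overstatement for a continuous marker is about 8 to 10 points for any cancer (33 to 22 cancers) and can reach 16 to 23 points for Gleason 7 or more (10 to 5 cancers). It is smaller for MRI. The direction does not depend on the AUC within 0.65–0.80. The size does depend on the number of cancers and the threshold rule, neither of which the protocol fixes. Specificity is not materially affected, and the primary prevalence estimate is untouched. The consequence is limited to the secondary accuracy results and the comparison of tests, which is enough to warrant a change before the data are analysed.

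**What to change.** 1. Before any data are analysed, name one analysis cut-off per test for the main accuracy report. Examples are the 3 ng/ml PSA value cited from the other study, one Likert score and one free to total PSA value. These are for analysis only and do not alter who is biopsied.
2. State that item 2 is reported at these cut-offs, for any cancer and for Gleason 7 or more, with confidence intervals.
3. Keep the thresholds derived under item 3, labelled exploratory, and name the rule that selects them. Report their sensitivity, specificity and net benefit after a bootstrap optimism correction that repeats the threshold search in each resample.
4. State the source of the probabilities used for calibration. If they come from a model fitted to these men, apply the same correction.

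The cost is a few sentences of wording and a few hours of programming. Reported sensitivity will be less favourable. Fixing the cut-offs removes the bias but not the imprecision that comes with few cancers.

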#### Harms

The conduct of the study will comply with all Israeli Health Ministry safety reporting requirements. All adverse experience reports must include the patient number, severity of reaction (mild, moderate, severe), relationship to study drug (probably related, unknown relationship, definitely not related), date and time of administration of test medications and all concomitant medications, and medical treatment provided. The principal investigator is responsible for evaluating all adverse events to determine whether criteria for “serious adverse events”, as defined above, are present. Investigators must notify the Rabin Medical Center Institutional Review Board (IRB) of all SAE and file the report in the regulatory study binder. Documentation from the IRB of receipt of these reportable events must be kept on file. A clear description of the suspected reaction should be provided along with an assessment as to whether the event is related to the study.

#### Auditing

The Data Safety and Monitoring Board (DSMB) will perform a planned audit 1.5 years from initiating the study. Regulatory agencies may also conduct a regulatory inspection of this study. Such audits/inspections can occur at any time during or after completion of the study. If an audit or inspection occurs, the investigator and institution agree to allow the auditor/inspector direct access to all relevant documents and to allocate his/her time and the time of his/her staff to the auditor/inspector to discuss findings and any relevant issues.

### Ethical matters

The study is conducted according to the principles of the declaration of Helsinki (2008) and the Medical Research involving Human Subjects Act (WMO), and has been approved by the Rabin Medical Center IRB. Written informed consent will be obtained from all patients before enrolment.

## Discussion

The only ongoing study specifically designed to test PSA screening among BRCA Carriers is the IMPACT study
[20,27]. The IMPACT study, led by [name], is a multicenter observational study of screening for prostate cancer. In this study, male BRCA carrier’s, 40 to 69 years old, are offered annual PSA testing and the threshold for prostatic biopsy is any PSA higher than 3 ng/ml. Recently, the first round of screening was published
[25]. In this study, a total of 199 men (8%) presented with PSA >3.0 ng/ml, 162 biopsies were performed, and 59 PCas were diagnosed (18 BRCA1 carriers, 10 BRCA1 controls; 24 BRCA2 carriers, 7 BRCA2 controls); 66% of the tumors were classified as intermediate- or high-risk disease. A final report is expected in 2018.

The proposed study, although targeting a similar population, is different in several important aspects. First, in the IMPACT study only patients with an elevated PSA level are offered a prostate biopsy. In a preliminary report on the first round of screening, only 8% had a biopsy
[25]. The fact that only such a small percentage of patients were offered a biopsy, and that it was offered based on PSA levels may cause a “verification-bias”
[27,28].

Verification bias is a type of measurement bias. This bias occurs when results of a screening test (i.e. PSA) affect whether a diagnostic test (i.e. prostate biopsy) is used. Results from the PCPT trial
[29], which offered prostate biopsy to all subjects (independent of their PSA level), demonstrated that as many as 15% of men with a PSA value less than 3.0 ng/mL had prostate cancer and that 15% of these cancers were high grade. These results may be even more pronounced in a population of high-risk men with germline mutations. To eliminate this bias, we will offer a prostate biopsy to all men included in the study regardless of the PSA level.

The second notable difference between our study and the IMPACT study is the target population. Our institution is located in Israel where the predominant BRCA mutations are the three founder mutations. There is evidence to suggest a genotype-phenotype difference among BRCA founder mutation carriers compared to other germ-line mutations
[30,31]. In addition, since 2% of Ashkenazi Jews carry one of the founder mutations we will have enough power to detect a difference in prostate cancer parameters between the three mutations
[31].

We also propose a more comprehensive preliminary screening compared to the IMPACT study. In our study the initial screening will include: DRE, PSA free to total PSA, a multi-parametric prostate MRI and a trans-rectal ultra-sound guided prostate biopsy. Thus, we will be able to determine the value of MRI screening, and determine the best screening modality. In breast cancer for instance, female BRCA carriers are advised to complete both mammography and MRI
[32]. Each of these screening tests provides valuable information and both are needed. The same may be true in male carriers.

We will also include a Benign Prostatic Hyperplasia (BPH) assessment: the validated International Prostate Symptom Score (IPSS), trans-rectal US assessment of prostate size, urine flow and residual. To the best of our knowledge, there is no data regarding the impact of these mutations on BPH. Since there is a prospect of identifying new biomarkers in this population we will also store whole blood, lymphocytes, serum, plasma, urine, and prostate tissue for future studies on all subjects.

In summary, this study protocol offers male BRCA carriers a complete prostate assessment including both cancer and BPH measurements. This is a very unique population and unlike most places in the world, Israel has a large proportion of BRCA carriers, as 2% of the Ashkenazi Jews are BRCA carriers. So far, male BRCA carriers are largely ignored. In biological research, the study of an unusual or rare event sometimes allows the identification of key features of more common forms. A good example of this has been the cloning and characterization of tumor suppressor genes in rare familial renal cell cancer. Data from this study will be used not only to understand the link between BRCA and prostate cancer risk. We will also store tissue, whole blood, serum, and urine for future studies that may aid our understanding of prostate cancer patho-physiology.

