### Study population

The target population is males carrying germline mutations in BRCA1 or BRCA2. Eligible men, carriers of one or more of the above mentioned mutations, will be identified through collaboration and under supervision of the genetic clinic in Beilinson hospital.

Individuals expressing interest in taking part in the study will be contacted by the research team and an initial appointment will be scheduled. The individual will be given the option to participate in the MRI and the prostatic biopsy. Fully informed written consent will be sought before collecting any research samples.

Inclusion criteria

• Male carrier of mutation in BRCA 1\2.

• Age 40–70 years.

• WHO performance status 0–2 (Additional file
1).

• No previous history of prostate cancer.

• No previous prostate biopsy.

• Absence of any psychological, familial, sociological or geographical situation potentially hampering compliance with the study protocol and follow-up schedule.

• Individuals that cannot undergo the MRI exam due to high creatinine level or claustrophobia will be excluded from the MRI part.

• Informed written consent must be sought according to ICH/EU GCP, before subject I inclusion.

Exclusion criteria

• Previous cancer with a terminal prognosis of less than five years.

• Previous prostate cancer.

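### The article promises to identify the best screening modality, but the accuracy analyses it names are per test, with no between-test contrast and no common set of men

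*Protocol article*

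**What the plan says.** The comparative claim is in the Discussion: after listing the initial tests and biopsy, the article concludes "Thus, we will be able to determine the value of MRI screening, and determine the best screening modality".

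The supporting analyses are in Secondary analysis:
- Item 2 plans "Sensitivity, specificity, positive and negative predictive value of: PSA, free to total PSA, prostate MRI in detecting prostate cancer".
- Item 3 says "A Receiver Operating Curve (ROC), and calibration and decision curve analyses will be performed for each of the aforementioned screening tests". It adds that a biopsy threshold for each test will be calculated for any cancer and for clinically significant cancer (Gleason sum 7 or higher).
- Item 4 says "We will use a Markov model to establish the cost effectiveness of different screening tests".

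Who has which test is set out in two places. Study population says "The individual will be given the option to participate in the MRI and the prostatic biopsy" and "Individuals that cannot undergo the MRI exam due to high creatinine level or claustrophobia will be excluded from the MRI part". First round of screening puts the creatinine limit at 1.8 mg/dl and gives the 12-core biopsy to men who agree to it. The same section adds a fusion-guided core when MRI shows a focal lesion that the standard 12 cores do not cover.

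The Methods paragraph of the Abstract, by contrast, describes PSA, free to total PSA, MRI and biopsy in all consenting men.

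**The concern.** Naming one modality as best is a statement about differences between tests. The accuracy analyses named would give three separate sets of estimates. Three difficulties follow.

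1. **Selection.** Cancer status is known only in biopsied men. Among them, PSA and free to total PSA should be available for all, but MRI only for those who chose it and were not excluded. Setting an MRI curve from the smaller set beside a PSA curve from the larger one mixes the effect of the test with the effect of who had it.
2. **Unused pairing.** Most men are meant to have every test, so results are correlated within a man. An interval for a difference should use that correlation, and separate curves do not supply one.
3. **Reference standard.** An MRI lesion can lead to an extra core. A cancer found only in that core counts as an MRI success and would have gone unrecorded without MRI. Men without MRI cannot receive that core.

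What is at stake is whether a reported ranking of PSA, free to total PSA and MRI reflects the tests, the men or chance.

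**Working it through.** **Claim against analysis.** The article states no sample size, power or effect size for comparing tests, so there is no figure of its own to reproduce. Set side by side:

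| Needed to name a best modality | What the article states |
|---|---|
| A between-test contrast in accuracy | None; measures and curves are per test |
| A common set of men | None; MRI and biopsy are optional, with some exclusions from MRI only |
| A criterion for best | None |
| A reference standard independent of the tests | 12 cores, plus a targeted core in some MRI-positive men |

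**Effect of case mix alone (assumed values).** Take one test with sensitivity 0.90 for high-grade and 0.50 for lower-grade cancer. If 30% of cancers in one set of men are high grade, overall sensitivity is 0.90 × 0.30 + 0.50 × 0.70 = 0.62. If 50% are, it is 0.90 × 0.50 + 0.50 × 0.50 = 0.70. The test is unchanged, yet the figures differ by 0.08.

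**Precision of a paired AUC difference (illustration).** Inputs:
- N = 220, the only number of men given for this study; Primary analysis uses it to trigger a preliminary analysis.
- 15% with cancer, the rate the article quotes from the PCPT trial for men with PSA below 3.0 ng/mL: 220 × 0.15 = 33.
- Clinically significant cancers, low case: the 15% high-grade share quoted from the same trial, 33 × 0.15 ≈ 5.
- Clinically significant cancers, high case: the 66% intermediate- or high-risk share quoted from IMPACT, 33 × 0.66 ≈ 22.
- Assumed: AUC A = 0.70 and correlation r = 0.3 to 0.5 between the two AUC estimates.

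Hanley-McNeil variance with n1 cases and n0 non-cases:

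Var = [A(1−A) + (n1−1)(Q1−A²) + (n0−1)(Q2−A²)] / (n1·n0),

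with Q1 = A/(2−A) = 0.5385 and Q2 = 2A²/(1+A) = 0.5765.

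For 33 against 187: [0.21 + 32 × 0.0485 + 186 × 0.0865] / 6171 = 0.00289, so SE = 0.054. The SE of a difference is SE × √(2(1−r)), and the 95% half-width is 1.96 times that.

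| Cases / non-cases | SE of one AUC | Half-width, r = 0.5 | Half-width, r = 0.3 |
|---|---|---|---|
| 33 / 187 (any cancer) | 0.054 | 0.105 | 0.125 |
| 22 / 198 (significant, high case) | 0.065 | 0.127 | 0.150 |
| 5 / 215 (significant, low case) | 0.133 | 0.260 | 0.308 |

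Varying the any-cancer prevalence at 220 men: 5% gives 11 cancers and a half-width of 0.18 to 0.21; 20% gives 44 cancers and 0.09 to 0.11.

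**Cross-check on sensitivity.** Assume true sensitivities of 80% and 60%, paired in the same men with cancer, and an exact two-sided McNemar test at 0.05. With discordant proportions 0.32/0.12 (independent results) or 0.25/0.05 (correlated), 33 cancers give power of 32% or 46%. Power of 80% needs 91 or 61 cancers. At 15% prevalence that is 91/0.15 ≈ 607 or 61/0.15 ≈ 407 men with both tests and biopsy.

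**The case against.** Several points on the other side carry weight.

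- **The design is essentially paired.** The Abstract has every man undergoing every test. A reader might infer that the tests will be analysed on different men, but no section says so. The MRI set is nested within the PSA set, and the imbalance follows only from optional consent and the MRI exclusions if no common set is imposed. This stands, and it makes the remedy easy.
- **The plan does set tests against each other.** Decision curves put each test's net benefit on one scale, and the Markov model compares strategies. So it would be wrong to infer that the plan cannot compare tests at all. But both would draw on the same per-test estimates, so neither removes the selection.
- **Method detail may sit in a document not shown.** The absence of a named paired test is therefore no error in itself. What remains is a firm conclusion in the article that its stated accuracy analyses do not reach.
- **A combined rule.** A reader might take "Each of these screening tests provides valuable information and both are needed" as a commitment to analyse PSA and MRI together. That sentence concerns mammography and MRI in women; the article adds only that the same may hold in male carriers. No objective or endpoint includes a combination, so its absence is not an error.
- **The precision figures are borrowed.** 220 is not a final sample size. The 15% rate comes from another population restricted to low PSA, and the article suggests carriers may fare worse. The 66% comes from a PSA-selected group that includes controls. Neither grade definition is shown to match Gleason 7 or higher. The figures illustrate scale and do not show that the study is too small.

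**Conclusion.** The concern holds in a limited form. The Discussion claims more than the named accuracy analyses deliver: they are per test, with no stated contrast, and as written MRI accuracy would be estimated in a self-selected subset of the men used for PSA. This affects what the trial can conclude about screening tests. It does not affect the primary prevalence estimate.

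At the one number of men the article gives, an AUC difference smaller than roughly 0.1 for any cancer would not be distinguishable from none. For clinically significant cancer the corresponding limit lies somewhere between about 0.13 and 0.31. These limits rest on 220 men, full uptake of MRI and biopsy, borrowed cancer rates, and an assumed AUC and correlation. A larger final sample would narrow them; lower uptake would widen them. The mismatch between claim and analysis does not depend on them.

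**What to change.** In Secondary analysis:

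1. Compare PSA, free to total PSA and MRI in the men who have all three tests and biopsy. Report paired AUC differences (DeLong) with 95% CIs.
2. Report paired differences in sensitivity and specificity (McNemar-type) with 95% CIs, at thresholds fixed in advance or corrected for optimism. Thresholds calculated from the same data would flatter the tests.
3. Use the same common set for the decision curves. Keep the estimates from all available men as a supplement.
4. State that an MRI lesion can lead to an extra targeted core, so the reference standard partly depends on MRI. Repeat the comparison using the standard 12 cores only; biopsy locations are already labelled for pathology.

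In the Discussion, replace the claim to determine the best modality with a statement that the study will estimate the differences in accuracy between the screening tests. A PSA-plus-MRI rule may be added as an option.

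The cost is modest extra analysis on data already being collected, with no change to study procedures. Men without MRI drop out of the comparison, which then applies to men able and willing to have MRI, and the claim becomes more modest.
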